## Abstract

Stunting predominantly occurs during the first 1000 days of life and continues to the age of five years. We will aim to assess the effectiveness of specialized nutritious foods (SNF)and social and behavior change communication (SBCC) strategies during the first 1000 days of life to prevent stunting among children in two rural districts of Badakhshan, Afghanistan. This will be a quasi-experimental pre-post study with the control group utilizing qualitative and quantitative methods. Before launching the program, formative research will be conducted on the acceptability, appropriate use and SBCC strategies needed to support the introduction of intervention package. Repeated cross-sectional baseline and endline surveys will be conducted in both the intervention and the control districts. After the formative research and baseline household survey, an intervention focusing on the provision of SNF, targeting pregnant and lactating women and children 6–23 months, and SBCC strategies will be implemented for at least 12 months. The primary outcome will be a reduction in the prevalence of stunting among children under two years in the intervention group compared to the control group. We will aim to compare the intervention and control group between the pre- and post-intervention assessments to isolate the effect of the intervention by difference-in-differences estimates. The program monitoring and evaluation component will examine the quality of implementation, acceptability of intervention, identification of potential barriers and to learn how to enhance the program’s effectiveness through ongoing operational improvements. The results will be beneficial to design interventions to prevent stunting within Afghanistan and other low–middle-income countries.

**Trial Registration:** Clinicaltrials.gov NCT04581993 [Registered: 8 October 2020].

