## 1. Introduction

Malnutrition is an indicator of social and political instability as it represents a multifaceted problem linked to poverty, food insecurity and poor hygiene and health [1]. Optimal infant and young child feeding (IYCF) practices including an early initiation of breastfeeding, exclusive breastfeeding for 6 months and the introduction of micronutrient-rich and age-appropriate complementary foods from 6 months are particularly important for ensuring the healthy growth and development of young children [2,3,4,5,6]. In 2020, an estimated 149 million children worldwide under five were stunted and 45 million were wasted [7]. The prevalence of undernutrition is significantly higher among unstable and conflict-affected settings [8]. Almost all the countries ranked within the highest 10% of the Global Hunger Index [9] and with the highest stunting rates are classified as unstable or conflict affected [10]. Afghanistan is the only country in the South Asia region in a conflict-affected and fragile situation [10,11]. Afghanistan also ranks 8th on the Global Hunger Index, 14th for stunting rate and 42nd of 45 countries by the Hunger and Nutrition Commitment Index on the country’s government’s political commitment to tackling hunger and malnutrition [9,12,13]. There is a growing evidence base of effective high impact interventions to reduce preventable malnutrition during the first 1000 days of life, between pregnancy and 24 months of age [1]. These include nutrition-sensitive and nutrition-specific interventions.

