### 1.3. Primary Outcome

The impact of nutritional supplementation during the ‘1000 days’ on the reduction in the prevalence of stunting (LAZ < −2 SD) among children under two years of age in the intervention areas compared to control areas.

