### 1.4. Secondary Outcomes

Impact on low birth weight (birth weight < 2500 g) by improving maternal nutrition.Impact on reduction in the prevalence of wasting (WLZ < −2 SD) and underweight (WAZ < −2 SD) in children under two years of age.Improvement in IYCF practices.Improvement in minimum acceptable diet and minimum dietary diversity among PLW.Improvements in care-givers’ knowledge, attitudes and practices related to infant and young child feeding.Improvement in mean hemoglobin concentrations in children and PLW.Improvement in maternal BMI z-scores.Formulation and adoption of local recipes for complementary feeding of children aged 6–23 months using locally available nutritious foods.

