## 2. Experimental Design

### 2.1. Study Design

A quasi-experimental pre-post study design with a control group will be used to evaluate the study outcomes. We propose to compare the intervention and control group between the pre- and post-intervention assessments to isolate the effect of the intervention by difference-in-differences estimates. Repeated cross-sectional baseline and endline surveys will be conducted in both the intervention and control districts. The intervention districts in province Badakhshan will be subjected to a robust implementation and close monitoring of the SNF provision, together with SBCC activities delivered through health facility staff, CHWs and mother care groups, while the control districts in province Takhar will receive the routine standard of care available in the area.

Before launching the intervention, formative research will be conducted on the acceptability and appropriate use of nutritional supplements and to help inform the SBCC strategies related to supplements, maternal diet during pregnancy and lactation and IYCF practices. A literature review will be conducted to adapt the relevant themes and existing national guidelines on maternal, infant and young child nutrition (MIYCN) to the local context of Afghanistan. Qualitative methods will be used for formative research including focus group discussions (FGDs) and key informant interviews (KIIs) with target population and relevant stakeholders and direct observations (DOs) for most common household foods recipes for the PLW and children aged 6–23 months.

Program monitoring, evaluation and learning will be conducted to examine the processes including the quality of implementation, the acceptability of the program components, the identification of potential barriers and to learn how to enhance the program’s effectiveness through ongoing operational improvements. This will be conducted by the AKU and study partners on a monthly basis to assess the distribution of supplements, the number of mother groups formed, the key SBCC messages delivered, food demonstrations, the development of local recipes, the monthly mother group meetings, the CHW meetings held on various SBCC activities and the identification of model families (Figure 1).

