## 6. Study Strengths and Limitations

The study will be among the first to evaluate the effectiveness of SNF targeting pregnant and lactating women and children aged 6–23 months and SBCC strategies on a reduction in the prevalence of stunting among children in Afghanistan.Program monitoring and evaluation data will allow us to examine the quality of implementation, the acceptability of intervention, the identification of potential barriers and to learn how to enhance the program’s effectiveness through ongoing operational improvements.The cohort of enrolled PLW and children will help to understand the feasibility and adherence to intervention within a community over a 12-month period.The quasi-experimental design limits the choice in the selection of study area and the random selection of health facilities.

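### At the 12-month minimum no endline child can have had the whole 1000-day package and about half had no exposure in pregnancy, so section 1.3 claims more than the estimate can show

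*Protocol article*

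**What the plan says.** - **Window.** The Introduction of the protocol article describes the "first 1000 days of life, between pregnancy and 24 months of age".
- **Primary outcome.** Section 1.3 reads "The impact of nutritional supplementation during the ‘1000 days’ on the reduction in the prevalence of stunting", assessed "among children under two years of age in the intervention areas compared to control areas".
- **Duration.** The Abstract places the intervention after the formative research and the baseline survey: "SBCC strategies will be implemented for at least 12 months". No maximum is given. Section 6 also mentions twelve months, but about what an enrolled cohort will show on feasibility and "adherence to intervention within a community over a 12-month period".
- **Evaluation.** Section 2.1 states: "Repeated cross-sectional baseline and endline surveys will be conducted in both the intervention and control districts". Section 3.4 makes mothers with children under two eligible and does not restrict the endline sample by date of birth.
- **Supplement windows.** Under section 1.2, women are supplemented through pregnancy and the first 6 months of lactation, and children from 6 to 23 months of age. Together these cover the whole window.
- **Birth weight.** Section 1.4 lists "Impact on low birth weight" as a secondary outcome, acting through better maternal nutrition. Section 4 refers to newborns. The article does not say which births supply the data.

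**The concern.** Window, target population and guaranteed duration do not fit together. The outcome credits an effect to supplementation during the 1000 days in every child under two. A programme that starts after baseline and may end 12 months later cannot have reached the older half of those children before birth. Supplementation in pregnancy is part of what makes this a 1000-day package and not only a complementary-feeding programme, and that part would be absent for those children.

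Interpretation is at stake. The results are meant to inform the design of stunting prevention in Afghanistan and similar countries. If they are reported in the words of section 1.3, a small or null difference could be taken as evidence against supplementation through the full window, which the survey would not have tested.

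**Working it through.** The duration is a design statement with no calculation behind it, so there is no planned figure to reproduce. The check is an overlap calculation.

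**Inputs from the article:** window from pregnancy to 24 months (Introduction); programme duration D of at least 12 months (Abstract); supplement windows (section 1.2); endline cross-section of under-twos (sections 2.1 and 3.4).

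**Assumptions:** pregnancy of 9 months, so a window of 9 + 24 = 33 months; ages uniform over 0-24 months; endline when the programme period ends; full coverage from the first day.

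**Formulas.** For a child aged *a* months at endline:

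- pregnancy months covered = min(9, D − a) if a < D, otherwise 0
- window months covered in total = min(D, a + 9)
- share with no pregnancy exposure = (24 − D)/24 for D up to 24

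**Exposure by age at D = 12:**

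| Age at endline (months) | Share of sample | Pregnancy months covered | Months covered in first half-year of life | Child-supplement months |
|---|---|---|---|---|
| 0-2 | 12.5% | 9 | all so far | 0 |
| 3-5 | 12.5% | 12 − a (9 down to 6) | all so far | 0 |
| 6-11 | 25% | 12 − a (6 down to 0) | 6 | a − 6 (0 up to 6) |
| 12-17 | 25% | 0 | 18 − a (6 down to 0) | a − 6 (6 up to 12) |
| 18-23 | 25% | 0 | 0 | 12 |

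**Results at D = 12:**

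- No pregnancy exposure: (24 − 12)/24 = 50%.
- Pregnancy fully covered: 3/24 = 12.5%. Partly covered: 9/24 = 37.5%.
- Mean pregnancy exposure: 0.125 × 9 + 0.375 × 4.5 = 2.8 of 9 months.
- Longest possible exposure: 12 of 33 months, or 36%.
- Mean window months covered: (31.5 + 252)/24 = 11.8, where 31.5 is the integral of a + 9 over ages 0-3 and 252 = 21 × 12. The mean window time already lived through is 12 + 9 = 21.0 months, so 11.8/21.0 = 56% is covered.

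**Sensitivity to duration:**

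| D (months) | No pregnancy exposure | Pregnancy fully covered |
|---|---|---|
| 12 | 50% | 12.5% |
| 15 | 37.5% | 25% |
| 18 | 25% | 37.5% |
| 21 | 12.5% | 50% |
| 24 | 0% | 62.5% |
| 33 | 0% | 100% |

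Covering every under-two from conception to endline takes 33 months. Slow roll-out or incomplete coverage would make the exposure shares worse than these.

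**The case against.** The best defence is that supplementation during the 1000 days naturally means support delivered within that window. Section 1.1 uses the phrase in that sense, and no passage promises any child coverage from conception to 24 months. On that reading the area-level difference-in-differences answers a sensible question about the programme as run. This stands. It is why the finding concerns what the estimate may be called, not whether it is valid.

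Several stronger readings are tempting, and the documents do not support them:

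- **That no child is exposed to the 1000 days.** Every endline under-two has some exposure inside the window. What cannot occur at 12 months is exposure to all of it.
- **That the primary question goes unanswered.** The contrast validly estimates the effect of about 12 months of programme on under-two stunting.
- **That half is a fixed figure.** Twelve months is a floor, and the share falls as D grows. Section 6 does not fix the interval from launch to endline.
- **That child supplementation is badly cut short.** Children under 6 months are ineligible for it at any duration. Mean child-supplement time at 12 months is (72 + 72)/24 = 6.0 months, and the most any duration could give this age mix is 162/24 = 6.75, so 89% is reached. The shortfall lies in pregnancy and early life.
- **That the sample size is too small because of dilution.** Section 3.4 does not say that its 13% reduction assumed full exposure.
- **That low birth weight suffers a calculable loss of power.** The article specifies no analysis that pools births from before launch with later ones, so the point is conditional.

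It can also be said that age-band and birth-cohort analyses belong in an analysis plan. Their absence from the article is not the finding. The finding is the mismatch between the outcome wording, the population and the duration that the article states.

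**Conclusion.** The concern holds in a limited form. At the stated 12-month minimum no endline child can have received the complete package. About half of the under-two sample would have had no exposure in pregnancy, and about one in eight a fully covered pregnancy. The primary estimate then averages different partial exposures: only maternal supplementation below 6 months of age, only the child supplement at 18-23 months, and mixtures between. It estimates the programme as delivered and not full 1000-day supplementation, which section 1.3 can be read to mean.

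The figures rest on uniform ages, full coverage from launch and an endline at exactly 12 months. The 50% falls to 25% at 18 months and disappears at 24. Even at 24 months some children would have had only part of the pregnancy covered.

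**What to change.** 1. Reword section 1.3, and the matching claim in the conclusion, to the effect on under-two stunting of the actual programme duration (at least 12 months) delivered within the 1000-day window.
2. Keep all children under two as the primary estimate.
3. Pre-specify a secondary difference-in-differences by birth cohort: endline children born before launch and those born after, each compared with the matching age band at baseline. At a 12-month endline the bands are 12-23 and 0-11 months. Because cohort and age coincide, a difference between the two results cannot be put down to pregnancy exposure alone and should be described as such. If an analysis plan already contains this split, only the rewording remains.
4. If birth weight is taken from surveyed under-twos, restrict the endline low-birth-weight analysis to births after launch, and say so.

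The cost is small: wording, plus one analysis that needs only date of birth and launch date. The downsides are a narrower claim and less precision within cohorts. With about half the sample in each at 12 months, standard errors would be up to about √2 = 1.4 times those of the overall estimate if the design effect stayed the same.

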## 1. Introduction

Malnutrition is an indicator of social and political instability as it represents a multifaceted problem linked to poverty, food insecurity and poor hygiene and health [1]. Optimal infant and young child feeding (IYCF) practices including an early initiation of breastfeeding, exclusive breastfeeding for 6 months and the introduction of micronutrient-rich and age-appropriate complementary foods from 6 months are particularly important for ensuring the healthy growth and development of young children [2,3,4,5,6]. In 2020, an estimated 149 million children worldwide under five were stunted and 45 million were wasted [7]. The prevalence of undernutrition is significantly higher among unstable and conflict-affected settings [8]. Almost all the countries ranked within the highest 10% of the Global Hunger Index [9] and with the highest stunting rates are classified as unstable or conflict affected [10]. Afghanistan is the only country in the South Asia region in a conflict-affected and fragile situation [10,11]. Afghanistan also ranks 8th on the Global Hunger Index, 14th for stunting rate and 42nd of 45 countries by the Hunger and Nutrition Commitment Index on the country’s government’s political commitment to tackling hunger and malnutrition [9,12,13]. There is a growing evidence base of effective high impact interventions to reduce preventable malnutrition during the first 1000 days of life, between pregnancy and 24 months of age [1]. These include nutrition-sensitive and nutrition-specific interventions.

Several complementary feeding strategies, including the use of specialized nutritious foods (SNF), have been shown to improve growth outcomes and reduce child stunting in food-insecure settings [14,15,16]. However, these findings show either modest improvements or mixed evidence, with declining rates of growth still observed among groups that receive food supplementation [17,18,19,20,21,22,23,24,25,26]. The evidence suggests that with thoughtful formative research and planning, behavior change communication (BCC) interventions can in fact positively improve infant and young child feeding (IYCF) practices, nutritional status and growth [27]. Current studies on the impact evaluations of large-scale BCC interventions to improve IYCF practices in several countries have shown that intensive interpersonal counseling combined with mass media and community mobilization activities have positive impacts on breastfeeding [28,29] and complementary feeding practices [28,30,31].

Worldwide, although investments have been made in implementing nutrition programs and generating robust evidence, peer-reviewed data are limited and program knowledge, often within the grey literature, is not widely shared or transferred. A 2018 series on nutrition in South Asia included two reviews, one on maternal nutrition interventions and another on optimal breastfeeding interventions. No studies from Afghanistan were eligible for these reviews to assess the effectiveness of program approaches to improve the coverage of maternal nutrition interventions and predictors of optimal breastfeeding among children 0–23 months [32,33]. However, there is a need to assess the effectiveness of SNF and social and behavior change communication (SBCC) strategies from Afghanistan to generate evidence for policy development and program implementation in the country and to be scaled-up in other fragile settings facing similar challenges.

### 1.1. Description of Stunting Prevention Programme

As part of the Country Strategic Plan, the World Food Program (WFP) planned to implement a stunting prevention program in collaboration with the Ministry of Public Health (MoPH) through its Public Nutrition Department, Afghanistan in two selected districts of Badakhshan with stunting rates (HAZ < −2SD) of >45% [34]. These two districts were considered based on high stunting prevalence, access to beneficiary communities, the existence of implementing partners providing complementary health/nutrition and security access to implementation sites. The program will emphasize an appropriate nutrition support in the ‘1000 days’ window of opportunity with special focus on proven effective nutrition interventions such as appropriate breast feeding, complementary feeding, micronutrient supplementation, malnutrition treatment and prevention and hand washing. This will, therefore, take the form of an integrated approach ensuring the targeted beneficiaries are supported to access nutrition assistance as well as other complimentary interventions provided in-kind by study partners and will be promoted through SBCC. The program will target pregnant and lactating women (PLW) and children aged 6–23 months, but will also engage fathers, grandfathers, grandmothers and community players that influence maternal, infant and young child nutrition (MIYCN).

The program will include monthly distributions of SNF for PLW and children aged 6–23 months and counselling for their mothers and caretakers on the appropriate use of SNF. All the trainings and SBCC messages will be developed based on formative research on the knowledge, attitudes, practices and barriers to optimal IYCF practices. During the project implementation, emphasis will be placed on the adoption of the locally formulated complementary foods as well as the application of knowledge and practices promoted through the SBCC activities as part of the exit strategy and ensuring a long-lasting impact of the project.

The program will be implemented within the health delivery structure involving monthly implementation and delivery of a package of interventions with the support of the MoPH and Aga Khan Health Services Afghanistan, who will facilitate implementation via the health facilities and at a community level through community health workers/volunteers by Aga Khan Foundation, Afghanistan. To be embedded in the health delivery system, the basic package of health services facilities will be the reference sites to support the provision of complementary services. Community based mechanisms such as mobile health teams (MHTs) and community health workers (CHWs) will support beneficiary access and link with health/nutrition services. MHTs will specifically be engaged where applicable to move services closer to beneficiaries at a community level. MHTs will work through CHWs and other community resource persons to mobilize targeted beneficiaries (PLW/caregivers) for services. Beneficiary support groups such as mother care groups will be formed and will be the smallest unit for delivery of the intervention package.

The stunting prevention program will focus on the 1000 days’ window of opportunity to promote appropriate IYCF practices among children in the Badakhshan Province of Afghanistan.

### 1.2. Intervention Package and Delivery Mechanism

The interventions will focus on the provision of SNF to eligible beneficiaries and SBCC messaging delivered through existing health systems, mobile health teams and CHWs at community levels. All children aged between 6–23 months will receive locally produced lipid-based nutrient supplement–medium quantity (LNS-MQ) and PLW will receive Super Cereal during the study.

*Super Cereal—Wheat Soya Blend with Sugar:* Super Cereal is prepared from heat-treated wheat and whole soya beans, sugar, vitamins and minerals by the WFP. This product is pre-packed and available in 1.5 kg packets. The WFP food safety and quality control unit is responsible for the quality assurance of the product during the program period. A monthly ration of 7.5 kg of Super Cereal (250 g per day) will be provided to pregnant women during pregnancy and to lactating mothers for the first 6 months [35].

*Lipid-based Nutrient Supplement–Medium Quantity (LNS-MQ):* LNS-MQ or Wawa Mum is made with heat-treated oil seeds, pulses, cereals, milk powder, sugar, vegetable oils, vitamins and minerals. Wawa Mum is manufactured from ingredients that are fresh, of good quality and free of foreign materials, infestations and substances hazardous to health. It does not contain any ingredients of animal origin, except dairy products. A daily sachet of 50 g of Wawa Mum will provide 255 Kcal. A monthly ration of 30 sachets will be provided to children during 6–23 months of age. The WFP food safety and quality control unit is responsible for the quality assurance of the product during the program period [36].

*SBCC:* The SBCC strategy will be determined by a literature review and formative research. A cascade training approach will be followed, involving an initial training of master trainers followed by training for each selected health facility staff and community health workers. The minimum qualification for master trainers will be 14th grade education with 2–3 years of experience in maternal and child nutrition. The training will provide information on IYCF practices, child and maternal nutrition and nutritional supplements. Lead mothers will work as facilitators with support from CHWs. Information and demo guides including IEC materials will be used, highlighting selected key messages based on the nutrition issues in the targeted community. To create awareness in the community and at the household level, female and male support groups will be formed and/or strengthened in the catchment areas of CHWs. Female CHWs will form female health committees and male CHWs will form male health committees in their catchment areas. Meetings of both groups will be arranged with the assistance of the community support group and health workers on a monthly basis for the dissemination of SBCC messages related to IYCF practices, child and maternal nutrition and the use of nutritional supplements. Separate sessions on health education for pregnant women, lactating mothers, mothers-in-law, fathers and fathers-in-law will be conducted through the community support groups in the intervention areas using educational materials (flip charts) on IYCF practices and maternal and child nutrition. Considering their important role in decision-making, male members of the family will be encouraged to actively participate in these sessions. The AKU monitoring and evaluation team will assess and monitor the SBCC messages using monthly post distribution visits at health facility and household levels (Table 1, Figure 1).

